# The protocol of the Oslo Study of Clonidine in Elderly Patients with Delirium; LUCID: a randomised placebo-controlled trial

**DOI:** 10.1186/s12877-015-0006-3

**Published:** 2015-02-10

**Keywords:** Delirium, Treatment, Clonidine, Drug therapy, Double-blind method, Aged, Therapeutic use, Adrenergic alpha-2 Receptor Agonists

## Abstract

**Background:**

Delirium affects 15% of hospitalised patients and is linked with poor outcomes, yet few pharmacological treatment options exist. One hypothesis is that delirium may in part result from exaggerated and/or prolonged stress responses. Dexmedetomidine, a parenterally-administered alpha2-adrenergic receptor agonist which attenuates sympathetic nervous system activity, shows promise as treatment in ICU delirium. Clonidine exhibits similar pharmacodynamic properties and can be administered orally. We therefore wish to explore possible effects of clonidine upon the duration and severity of delirium in general medical inpatients.

**Methods/Design:**

The Oslo Study of Clonidine in Elderly Patients with Delirium (LUCID) is a randomised, placebo-controlled, double-blinded, parallel group study with 4-month prospective follow-up. We will recruit 100 older medical inpatients with delirium or subsyndromal delirium in the acute geriatric ward. Participants will be randomised to oral clonidine or placebo until delirium free for 2 days (Diagnostic and Statistical Manual of Mental Disorders (DSM-5) criteria), or after a maximum of 7 days treatment. Assessment of haemodynamics (blood pressure, heart rate and electrocardiogram) and delirium will be performed daily until discharge or a maximum of 7 days after end of treatment. The primary endpoint is the trajectory of delirium over time (measured by Memorial Delirium Assessment Scale). Secondary endpoints include the duration of delirium, use of rescue medication for delirium, pharmacokinetics and pharmacodynamics of clonidine, cognitive function after 4 months, length of hospital stay and need for institutionalisation.

**Discussion:**

LUCID will explore the efficacy and safety of clonidine for delirium in older medical inpatients.

**Trial registration:**

ClinicalTrials.gov NCT01956604. EudraCT Number: 2013-000815-26

## Background

### Delirium in hospitalised medical patients

Delirium commonly affects older people with acute medical illness [1,2]. It is associated with patient distress, increased length of stay, higher risk of new institutionalisation, higher mortality, and an increased risk of future dementia [3-6]. Despite its impact, delirium remains poorly understood and few treatment options are available.

The prevalence of delirium is at least 15% in hospitalised medical patients [7-9]. In patients with dementia the prevalence is even higher, being up to 50 % in medical wards [10]. Old age and pre-existing cognitive impairment are the most important predisposing factors for delirium [1,9], but, in principle, any acute medical condition can precipitate delirium in a vulnerable individual [7]. Subsyndromal delirium is a clinical condition that falls on a continuum between no symptoms and delirium defined by the Diagnostic and Statistical Manual of Mental Disorders-5 (DSM-5) [11]. Subsyndromal delirium may progress to full-scale delirium, and is a clinically important condition associated with poor outcomes. Efforts to prevent, detect and treat subsyndromal delirium are thus justified.

### Pathophysiology of delirium

The pathophysiology of delirium remains poorly understood. Leading hypotheses focus on neurotransmission, inflammation and acute stress as possible mechanisms [12]. Decreased cholinergic activity and increased dopaminergic activity in the central nervous system (CNS) are commonly postulated, with these neurotransmitter deficits resulting from multiple precipitants. A causal association between inflammation (pro-inflammatory cytokines) and delirium has also been proposed [13,14]. Another hypothesis implies that delirium may be the result of aberrant stress responses [13] as delirium commonly follows stress (physical or psychological). And whilst stress responses are adaptive in young people, they might be altered with ageing, leading to exaggerated and more prolonged stress responses. This hypothesis would also imply alterations of autonomic nervous system activity in patients with delirium [15].

### Pharmacological treatment of delirium

The hyperactive form of delirium is frequently treated pharmacologically, but the effect of different treatment modalities is poorly studied. The drug treatment of hypoactive delirium has hardly been evaluated at all. Thus more research on pharmacological treatment options for delirium is urgently needed. Haloperidol [16,17] and other antipsychotics (olanzapine [18], risperidone [19] and quetiapine [20]) are commonly used, and there is some, although weak, evidence of their efficacy [21,22]. There is no evidence on the effects of antipsychotics in patients with delirium superimposed upon dementia. For patients with parkinsonism or dementia with Lewy bodies, antipsychotics are generally avoided, leaving even fewer treatment options for these patients.

Antipsychotics have several drawbacks, including an increased risk of death and cardiovascular events, sedation, falls risk, and cognitive impairment [23]. These risks increase with age, dementia and disability. This calls for special caution for patients with delirium superimposed on dementia [21]. Benzodiazepines and other sedatives are also frequently used, but the evidence supporting these agents is even weaker [24]. There is no clear evidence for the efficacy of cholinesterase inhibitors in the treatment of delirium [25-27].

### Alpha-2-adrenoreceptor agonists

Dexmedetomidine and clonidine are both alpha-2-adrenoceptor agonists activating presynaptic inhibitory alpha-2-adrenoreceptors. Clonidine is a partial agonist with an alpha-2a-to-alpha-1 selectivity ratio of 39. For dexmedetomidine this ratio is 1300 [28]. They exert a general inhibitory influence on the sympathetic nervous system, in particular due to CNS effects [29]. Dexmedetomidine decreases sympathetic activity and attenuates the hemodynamic and neuroendocrinal stress responses (including of cortisol), resulting in decreased heart rate (HR) and blood pressure (BP) as well as sedative and analgesic effects [30]. In the intensive care setting, both substances reduce the need for opioids and sedatives [31]. Dexmedetomidine is increasingly used in intensive care patients, and is also used as an adjuvant during regional anaesthesia. Recently conducted studies indicate that the incidence of delirium is lower in intensive care patients receiving dexmedetomidine than in those receiving benzodiazepines [32,33], propofol [34] or morphine [35]. Currently available evidence thus suggests that dexmedetomidine may have value in the prevention and treatment of delirium in the intensive care unit [36,37]. Indeed, it is now in clinical use in the USA and Europe [38].

Most patients with delirium are however treated outside of intensive care units, where intravenous use of dexmedetomidine is not feasible. An alternative agent might thus be orally administred clonidine, which has very similar pharmacodynamics to that of dexmedetomidine [31], even though its alpha-2 selectivity is somewhat lower [28]. Clonidine additionally has an independent stimulatory effect on the parasympathetic activity and a slight anti-inflammatory effect [39,40], further making it an interesting candidate for delirium treatment. This does also accord with the hypothesis of delirium as a consequence of aberrant stress responses [13].

### Clinical experience with clonidine

Clonidine has been used as an anti-hypertensive drug for decades, as well as for anesthesia-related applications, such as perioperative analgesia [29,41], sedation and anxiolysis, and for management of both acute postoperative, chronic and neuropathic pain [41-43]. In one study, use of intravenous clonidine after surgical correction of acute type-A aortic dissection reduced the severity of delirium, improved the respiratory function and shortened the length of stay in the intensive care unit [44].

The adverse effects of clonidine include orthostatic hypotension, bradycardia and AV-block. Such effects are, however, dependent on dosage. In a previous report, low-dose treatment (75 μg) in healthy adults was associated with a reduction in heart rate from 72 beats/min to 63 beats/min, and a reduction in mean arterial pressure (MAP) from 88 mmHg to 75 mmHg. Less than 50% experienced sedation, dry mouth or dizziness, and for those who reported any of these side-effects, the severity was mild [45]. Clonidine has been studied in outpatients with Alzheimer's dementia [46,47] and in patients with Parkinson's disease [48,49]. Treatment with daily doses of clonidine less than 200 mcg was well tolerated in these patients. Relative contraindications to clonidine for its licensed indications include bradyarrhythmias, polyneuropathy, renal insufficiency and evidence of reduced cerebral and/or peripheral circulation due to vessel disease

### Pharmacokinetics of clonidine

Maximum plasma concentration (Cmax) following oral administration occurs after 1–3 h [45] and reduction in mean arterial pressure as well as the risk of side effects is highest at this peak. Cmax and area under the concentration-time-curve (AUC) increase proportionally with increasing doses. Clonidine traverses the blood–brain-barrier. The half-life during the elimination phase shows great inter-individual variation and is found to be between 5 and 25.5 hours. The metabolism is hepatic and the metabolites are inactive. Clonidine is mainly excreted renally (70%).

### Rationale for dosage plan of clonidine

A dosage plan for clonidine is presented in Table 1. Because we are studying short-term use in an acute setting, we want to achieve steady-state (serum concentration levels) more quickly by using loading doses (day 1) under close monitoring of blood pressure. On days 2–7 we will administer a lower maintenance dose. We will thus give 75 μg clonidine every 3^rd^ hour up to a maximum of 4 doses on day 1, and then 75 μg twice per day.

**Table 1 Tab1:** **Dosage plan for clonidine**

Time	Safety	Dosage
Day 1	Systolic BP has to be >120 mmHg before the first loading dose.	75 μg every 3^rd^ hour until maximum 4 doses, (e.g.: at 2, 5, 8 and 11 p.m)
Loading doses	If systolic BP is <100 mmHg, HR <50 beats/min, or if RASS is −3 or less before any of the subsequent loading doses, no more study medication will be given until the planned maintenance dose the next morning.	
	If RASS is −2, the treating physician has to assess if IMP will be given or not	
Day 2-7	If systolic BP is <100 mmHg, HR <50 beats/min, or if RASS is −3 or less just before a planned dose, no study medication will be given until the next planned dose 12 hours later.	75 μg BID, at 8–9 a.m and 8–9 p.m
Maintenance doses		
	If RASS is −2, the treating physician has to assess if IMP will be given or not	

Concentration levels of clonidine known to have clinical effects range from 0.2 to 2.0 ng/ml [50-52]. We are aiming for the lower levels, that is, between 0.3 ng/ml (median trough concentration) and 0.7 ng/ml (maximal concentration), because higher plasma concentration levels increases the risk of adverse events, including hypotension. Nonetheless, lower plasma concentration levels may be insufficient to give a significant effect on our primary endpoint.

To our knowledge, there are no studies of the relationship between plasma concentration of clonidine and delirium. In publications on the effect on delirium of dexmedetomidine, the plasma concentration levels are not reported. Additionally, dexmedetomidine is approximately 8 times more selective (alpha 2 versus alpha 1) than clonidine [28,31], and so pharmacokinetic data on dexmedetomidine cannot be used to estimate effective doses of clonidine. We thus have to extrapolate from pharmacokinetic data on clonidine used for other purposes. We know that clonidine has both sedative and anxiolytic effects, and that these centrally mediated effects are closely related to plasma concentration levels [53,54].

In a study of adolescents with chronic fatigue syndrome, a dosage of 50 μg twice per day resulted in a median trough concentration (C_0_) at 0.21 μg/L after 14 days of treatment, rising to a median level of 0.41 μg/L (C_max_) two hours after administration of one regular dose of 50 μg [55,56]. In a study of healthy normotensive subjects, treatment with oral clonidine 225 μg daily for one week resulted in a steady state of 0.3-0.35 ng/ml. After intake of one 75 μg tablet, the serum level then increased to 0.7 ng/ml at 2 h. There was a significant relationship between the plasma level of clonidine and sedation [53]. In subjects receiving oral clonidine 100 μg twice per day for 6 weeks, plasma concentration ranged between 0.4 and 0.7 ng/ml (levels 2 hours after intake of 100 μg) [52]. Another study found that a single dose of 75 μg gave a Cmax of 0.66 ng/ml after achieving steady-state with two 75 μg doses [57].

The present patient population (elderly with a glomerular filtration rate [GFR] limit of > 30 ml/min) may have a longer half life of clonidine due to a diminished renal capacity as compared to younger. Altough the metabolism of clonidine is hepatic, varying amounts of unmetabolised clonidine is secreted renally. Consequently, patients may also have a higher risk of adverse events related to the study drug. We therefore choose a lower dosage, considered safe, of 75 μg twice per day.

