**Table 4 Tab4:** **Diagnostic algorithm for DSM-5 delirium**

DSM-5 criteria	Tests to be performed or information needed			DSM-5 criteria fullfilled?	
				YES	NO
A. Disturbance in attention (i.e., reduced ability to direct, focus, sustain, and shift attention) and awareness (reduced orientation to the environment).	**Evaluation**	**TEST**	**Cut off (definition of inattention)**		
	**Daily**	Digit span forward	Less than 5 forward		
	**Daily**	Digit span backward	Less than 3 backwards		
	**Daily**	SAVEAHAART	2 or more errors		
	**Initial diagnosis only**	Days of the week in reverse order	Any error		
	**Initial diagnosis only**	Months of the year in reverse order	Unable to reach July		
	**Initial diagnosis only**	Count backwards from 20 to 1	Any error		
	Observation (by the examiner):				
	Distractibility. Comprehension. Tendency to lose the tread of conversation				
	The “DelApp” [level of arousal test followed by counting of serially-presented lights. Cut-off 7/8 out of 10]				
B. The disturbance develops over a short period of time (usually hours to a few days), represents a change from baseline attention and awareness, and tends to fluctuate in severity during the course of a day.	Informant history from patient´s carers and nursing staff				
	Questions to carer/ nursing staff or derived from clinical notes:				
	Has there been a sudden change in the patient´s mental state?				
	Does the patient seem to be better at any period in the day compared to other times?				
	Has the level of consciousness been altered (drowsy/not interacting or agitated)?				
	Sleep-wake cycle disturbances?				
C. An additional disturbance in cognition (e.g., memory deficit, disorientation, language, visuospatial ability, or perception).	Questions to the patient:				
	Orientation to time, place and person				
	Recall (3 words)				
	Why are you in hospital? Will a stone float in water? Are there fish in the sea? (any error = disorganised thinking)				
	Questions to carer/ nursing staff or derived from clinical notes:				
	Has there been any…:				
	Perceptual disturbances? Sleep-wake cycle disturbances? Memory disturbances? Psychotic symptoms?				
	Psychomotor abnormalities?				
D. The disturbances in criteria A and C are not explained by another preexisting, established, or evolving neurocognitive disorder and do not occur in the context of a severely reduced level of arousal, such as coma.	Information from history/chart/clinical assessment				

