### Evaluating patient eligibility

According to the inclusion and exclusion criteria, ECG, creatinine/eGFR, body weight and blood pressure measurements are required. The final decision on eligibility will be agreed with the treating physician on the ward. Capacity will be assessed and informed consent (and/or) assent obtained (see below).

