**Inclusion criteria**

All of the following conditions must apply to the prospective patient at screening prior to receiving study agent:Patient > 65 years old admitted to the acute, medical, geriatric wardDelirium or subsyndromal delirium within the last 48 hoursSigned informed consent from patient or relatives and expected cooperation of the patients for the treatment and follow up must be obtained and documented

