**Exclusion criteria**

Patients will be excluded from the study if they meet any of the following criteria:Symptomatic bradycardia, bradycardia due to sick-sinus-syndrome, second- or third- degree AV-block (if not treated with pacemaker) or any other reason causing HR <50 bpm at time of inclusion [44].Symptomatic hypotension or orthostatic hypotension, or a systolic BP <120 at the time of inclusionIschemic stroke within the last 3 months or critical peripheral ischemiaAcute coronary syndrome, unstable or severe coronary heart disease (symptoms at minimal physical activity; NYHA 3 and 4) and moderate to severe heart failure (NYHA 3 and 4). (Acute coronary syndrome is defined according to international guidelines)A diagnosis of polyneuropathy, phaeochromocytoma or renal insufficiency (estimated GFR < 30 ml/min according to the MDRD formula) [44]Body weight <45 kgConsidered as moribund on admissionUnable to take oral medicationsCurrent use of tricyclic antidepressants, monoamine reuptake inhibitors or ciclosporinPreviously included in this studyAdverse reactions to clonidine or excipients (lactose, saccharose)Not speaking or reading NorwegianAny other condition as evaluated by the treating physician

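### Table 1 withholds study drug at RASS −3 or less before every dose except the first, and no eligibility criterion sets a RASS limit in its place

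*Protocol article*

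**What the plan says.** Table 1 treats the first loading dose separately from the rest. Its condition for that dose is "Systolic BP has to be >120 mmHg before the first loading dose". For systolic BP below 100, HR below 50 or RASS −3 or less, the day-1 rule is worded "before any of the subsequent loading doses, no more study medication will be given until the planned maintenance dose the next morning". On days 2–7 the same three limits each postpone a maintenance dose by 12 hours. In both blocks a separate line says that at RASS −2 "the treating physician has to assess if IMP will be given or not"; on day 1 that line is not tied to the later doses.

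At entry, the exclusion criteria bar systolic BP below 120 and "any other reason causing HR <50 bpm at time of inclusion". None of the inclusion or exclusion criteria gives a RASS value. Under Evaluating patient eligibility, "ECG, creatinine/eGFR, body weight and blood pressure measurements are required"; RASS is not listed there, although the section on diagnosis says it is assessed. Low arousal at entry is limited only without a score:

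- DSM-5 criterion D in Table 4, also required for subsyndromal delirium, asks that the disturbances "do not occur in the context of a severely reduced level of arousal, such as coma".
- Patients who cannot take oral medication are excluded.
- The inclusion criteria ask for "expected cooperation of the patients for the treatment and follow up".
- The treating physician must agree on eligibility and may exclude for other conditions.

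**The concern.** The plan regards RASS −3 as too low an arousal level for giving this drug, because it withholds every later dose there. Yet it states no such limit for the dose that starts exposure. As written, a patient at RASS −3 could receive capsule 1 and be refused capsule 2 three hours later in an unchanged state.

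The plan itself describes clonidine as sedative, with that effect closely related to plasma level, and expects that its elderly patients may be at higher risk of adverse events. What is at stake is the consistency of a safety rule that ward staff must apply on day 1. No statistical quantity is at stake.

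**Working it through.** There is no figure in the plan to reproduce. The check is to list every fixed limit by time point (Table 1, Exclusion criteria, Diagnosis of delirium and subsyndromal delirium).

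| Time point | Systolic BP | Heart rate | RASS |
|---|---|---|---|
| Inclusion | below 120 excluded | below 50 excluded | assessed at diagnosis; no limit |
| Loading dose 1 | must exceed 120 | no fixed limit | −2: physician decides; −3 or less: no rule |
| Loading doses 2–4 | held below 100 | held below 50 | −2: physician decides; −3 or less: held to next morning |
| Maintenance, days 2–7 | held below 100 | held below 50 | −2: physician decides; −3 or less: held 12 hours |

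Three things follow.

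1. Blood pressure is checked at entry and again before capsule 1. For BP the plan therefore does not rely on the entry check alone.
2. Heart rate has a fixed limit at entry but not at capsule 1. The only opening is a new fall below 50 between inclusion and the first capsule, an interval the article does not state.
3. RASS −3 has no fixed limit at either point. Because the −2 line can be read as covering dose 1, the milder state has an instruction and the deeper one has none. That points to a wording slip.

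Coverage by count: 4 loading doses + 6 days × 2 maintenance doses = 16 planned doses at most. The RASS hold covers 3 + 12 = 15. This count locates the gap; it does not measure risk.

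Size of the uncovered exposure:

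- Dose: 75 / 300 = 25% of the day-1 maximum.
- Peak: the Loading doses section cites a Cmax of 0.29 ng/ml after a single 75 μg dose. The target range is "between 0.3 ng/ml (median trough concentration) and 0.7 ng/ml (maximal concentration"). Comparing peak with peak, 0.29 / 0.7 = 0.41.
- Effect: in the cited report on healthy adults at 75 μg, fewer than half had sedation, dry mouth or dizziness, and these were mild.

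The number of patients likely to enter at RASS −3 or less is not given and cannot be derived.

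**The case against.** The strongest reply is that different rules for first and later doses make sense. Before capsule 1 no study drug is on board, so low arousal reflects the delirium or its cause; the later holds control the response under exposure. The BP limits also differ between first and later doses, and the trial wants hypoactive patients. This shows that starting at RASS −3 could be a deliberate choice, but the text does not make it one. The later holds do not ask about cause, so a patient at −3 from delirium alone would still lose doses 2–4. A plan content to start at −3 would also hardly ask for judgement at −2.

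The second reply is that several safeguards already act: criterion D, oral intake, expected cooperation, physician agreement and RASS at diagnosis. This stands as a limit on size. None of them sets a threshold at −3, and most act at entry, in a condition that fluctuates.

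The third reply is that a condensed article may leave dosing checks to the full protocol. That would answer a missing detail. Here the article prints the dosing rule dose by dose, and the objection is to the rule as stated.

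A reader might infer more than the documents support, in three ways:

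- That HR below 50 is an equal gap. It is not: it is an exclusion at inclusion, an ECG is required for eligibility, and Monitoring and safety provides for individual management of bradycardia.
- That one capsule takes the patient to 97% of the target floor (0.29 / 0.3). That sets a single-dose peak against a median trough and is not a like-for-like comparison.
- That deeply drowsy patients will be dosed automatically. The plan does not require the first capsule to be given at −3; it only fails to say that it is withheld.

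**Conclusion.** The point holds as a minor inconsistency in a stated safety rule. RASS −3 or less stops loading doses 2–4 and all maintenance doses, but has no fixed limit before the first loading dose or at entry. The exposure at issue is at most one 75 μg capsule, with a cited peak about 41% of the plan's ceiling, and in the placebo arm it contains no drug. Affected patients are probably few, given the entry filters; that is a judgement, since no count is available. The cited peak comes from a study outside this population, and the plan allows that its own patients may eliminate clonidine more slowly. Nothing here affects power, the MDAS endpoint or the analysis. It is worth correcting because the correction is cheap.

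**What to change.** Reword the day-1 RASS hold in Table 1 to apply *before any loading dose, including the first*, and do the same for the HR hold for consistency. Keep the consequence Table 1 already has: no study medication until the next morning's planned dose. A retry at the next 3-hourly time would be inconsistent, since a withheld dose 1 would be retried the same day while a withheld dose 2 waits until morning.

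Two details need stating:

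- The systolic BP >120 condition should attach to whichever capsule is the patient's first. Otherwise a deferred patient would start under the maintenance rule, which holds only below 100.
- Deferring capsule 1 omits all four loading doses, and Criteria for patient discontinuation lists missing more than three consecutive doses as a reason to stop. Loading doses withheld under this rule should not count towards it.

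The patient stays randomised and in the intention-to-treat analysis.

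The cost is a short edit to Table 1 and one clarifying clause. RASS is already assessed at diagnosis, and Table 1 already needs HR and RASS before doses 2–4. The real downside is reduced loading, up to the full 300 μg on day 1, in a few deeply hypoactive patients, a subgroup the trial wants to study.
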